### Other assessments

#### Estimation of an individual's food intake during shared plate eating

Shared plate eating is a reality in many LMIC, and yet there are currently no methods available to accurately estimate the food and nutrient intake of individuals in that setting. This contributes to a large nutritional data gap. In this study, in addition to using Foodcam, we will employ a vision-based approach, which integrates face recognition, hand detection, and food recognition, using a 360° camera (35). A 360° camera will be set up in selected households where shared plate eating is practiced to capture video sequences of the eating. The use of a 360° camera reduces the burden of setting up multiple cameras to capture the eating episode. The vision-based approach uses deep learning techniques to recognize faces, detect hand movement and food items on a plate/bowl, and relate the food items consumed to an individual within a group. It can then estimate each individual's food intake by analyzing the hand–food interactions and the variation of hand–face distance of each individual throughout the eating.

#### Assessment of food acquisition and other food-related activities

Continuous, passive capture of images during the day provides a window into the daily activities of an individual. These activities could include food sourcing, food storage, preparation, cooking, eating, and feeding other household members. This study will not be using devices with GPS (Global Positioning System) functions due to concerns of land ownership/grabbing in some communities. However, the sequence of images captured by the devices during the course of the study is enough to provide information about where individuals in the households are obtaining their daily foods, such as buying from local markets, obtaining from household farm/garden, using food stocks in the household storage facilities, and so forth. The AIM software can collate all the images captured in a day and annotate them for the various food-related activities. In addition, an AI technology (36) that sequences images captured in a day (>10,000 images per individual per day) will also be used in this study. The images captured will be fed into commercial image labeling AI software (Clarifai). For each image, the AI software produces 20 words to describe what is on the image. We will then utilize a statistical analysis program to determine the activity on the image (i.e., food consumption or other food-related activities such as shopping, etc.). Our initial experiments on AI detection of food intake and related activities such as shopping and food preparation showed an overall accuracy and specificity of 91.5% and 86.4%, respectively, based on 3900 images ([name], [name], [name], unpublished results, 2019).

### Analytical plan

The data analysis plan will be based on comparison of dietary intake estimated using weighed food records, 24-h dietary recall, and the passive dietary assessment method. This will be achieved using the concordance correlation coefficient (CCC) of Lin et al. (37) to assess the extent of agreement in portion size estimation, daily intakes of energy, and macronutrient (carbohydrate, protein, fat, and selected fatty acids) and micronutrient (iron, zinc, vitamins A, B, D, iodine, folate, and calcium) estimates between methods. These comparisons will include the extent of agreement between the passive method compared with weighed food records, and 24-h dietary recall compared with weighed food records. A 95% CI will be calculated for each Lin CCC. The bootstrap method will be used to test whether the Lin CCC between weighed food records and the passive method is different from that between the weighed food records and 24-h dietary recall methods. In addition, Bland–Altman analysis will be used to assess the limits of agreement and examine trends in differences between methods as a function of magnitude of the value, and paired *t* tests will be used to compare the overall bias between method pairs. The passive and 24-h recall methods will be considered accurate when their estimates of nutrient intake are within ±10% of the intake value measured using weighed food records. The analyses will be conducted among the index cases and then stratified by child and adult, rural and periurban/urban, respectively. To explore factors related to the accuracy of the passive and 24-h recall methods compared with weighed food records, absolute or relative deviation, as appropriate, from the weighed food method (gold standard) will be used as an outcome and be analyzed using multiple linear regression (MLR). Candidate predictors in this MLR analysis include demography, education, urban/rural, child or adult.

Currently, we do not have an analysis plan for validation of the data on breastfeeding frequency and duration captured by the eHAT device because there are no comparable analytical methods. However, the use of the device in this study will help us to understand its acceptability and challenges, and help to inform future studies.

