#### Study 2: Evaluation of the feasibility and acceptability of passive dietary assessment devices in households in Ghana and Uganda

The purpose of this study is to evaluate the feasibility, acceptability, and performance of passive assessment devices in capturing food acquisition, preparation, and intake of households in Ghana and Uganda. In addition, this study aims to collect information on household structure, food, and eating behavior through an in-depth household interview, to inform the configuration and deployment of the camera devices appropriate for the food environment and eating culture of households in Ghana and Uganda.

Twenty-eight households (14 in each country) will be recruited and enrolled into the study. Prior to the recruitment of households, comprehensive community engagement meetings will be held with the community liaison office of the host institution, area government nutrition and health offices, community elders, and members of the communities to discuss the study and the use of camera devices to capture images of household food acquisition, preparation, and intake. Concerns raised by the communities will be addressed before the recruitment of households or start of the study.

Community elders and local field staff will help in identifying households for recruitment. Households will be enrolled when they meet these inclusion criteria: *1*) has ≥1 parent (mother or father); *2*) has a child or children aged <5 y and/or adolescent child/children (aged 10–19 y); *3*) members of the household eat the same prepared meal (i.e., each member does not prepare and eat separately); and *4*) willingness to use camera devices to record food preparation and intake. Enrollment of households will be through the household head or the primary food preparer, other adults in the households, and assent of teenagers.

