#### Study 3: Assessment of the validity of passive assessment method in estimating dietary intake in households in Ghana and Uganda

The purpose of this study is to test the validity of passive dietary assessment method relative to a weighed food record, in estimating an individual's dietary intake. The weighed food record is used as the gold standard method in this study. A tablet-based, interviewer-administered multiple-pass 24-h dietary recall will also be performed for comparison. Portion size picture aids will be used in the 24-h dietary recall.

Local field staff and community leaders will help in identifying 88 households (44 in each country) for enrollment in this study. The criteria for inclusion are the same as those described for Study 2. Foodcam will be mounted in the household's kitchen or cooking area to capture images of food preparation. Household members will be given a camera device to record their whole-day (waking hours) food intake, and the captured images will be used in the estimation of their dietary intake. However, only 2 randomly selected index cases (an adult and a child) in each household will have their corresponding dietary intake assessed using weighed food records and 24-h dietary recall. Dietary intake data from the devices and the 24-h dietary recall will be compared with weighed food records for accuracy evaluation. Prior to using the devices in the households, a questionnaire (similar to that used in Study 2) will be used to understand the structure, composition, and eating habits of the households to help implement a device deployment plan, especially for those who were not recruited in Study 2. To help recognize and effectively manage the data collection and logistical challenges that might arise in this study, this validation study will be conducted in 2 phases:

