*Phase 1: Pilot testing of the validation protocol in a sample population*. This phase is aimed at testing the study protocol in a sample of the households to help identify and address challenges that might arise during the data collection process. Study teams in the 2 countries will recruit 8 households each (16 households in total) for this purpose. The camera devices will be set up to record food preparation and intake in the households for a day. On the same day, the meals of the 2 index cases in each household will be weighed before and after eating. On the next day, a staff member not involved in the data collection on the previous day will visit the households to complete the multiple-pass 24-h dietary recalls—a method comprising multiple and sequential layers of questioning to increase accuracy in the reported food intake. The primary caregiver will complete the recall data for smaller children (especially those aged <5 y).

Data from the devices, weighed food record, and 24-h recall will be uploaded onto the cloud-based study database. These data will help determine the fidelity of the study protocol, robustness of the image capture and data transfer, identify challenges, and help inform any potential amendments to the protocol before the validation study in the target population.

*Phase 2: Validation in the target population*. In this phase, the passive dietary assessment devices will be validated in 88 households in the 2 countries. The devices will be set up to record food preparation and intake in the recruited households for 3 nonconsecutive days, preferably 2 weekdays and a weekend day. On each day, study staff will visit the households in the morning to mount the Foodcam in the kitchen/cooking area and help members of the household wear their devices. The devices will record an individual's food intake for the whole day during waking hours. At the end of each day, staff will return to the households to collect all the devices. In addition, the same staff will weigh and record the food intakes, before and after eating, of the index cases for the weighed food record measurement. After each day, a different staff member will visit the households to complete the 24-h dietary recall for the index cases.

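### Independent-data methods are named for data nested in households and days without fixing the unit of analysis, so naive standard errors in the pooled analyses would be too small

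*Protocol article*

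**What the plan says.** **Design (Study 3).** In Phase 2, "the passive dietary assessment devices will be validated in 88 households in the 2 countries". The devices run "for 3 nonconsecutive days, preferably 2 weekdays and a weekend day". The weighed record and the recall are taken on "only 2 randomly selected index cases (an adult and a child) in each household". On eligibility, "The criteria for inclusion are the same as those described for Study 2", and one Study 2 criterion is that "members of the household eat the same prepared meal".

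**Analysis (Analytical plan).** Agreement in portion size and in daily energy and nutrient intakes is measured by Lin's concordance correlation coefficient (CCC), for passive against weighed and for recall against weighed. "A 95% CI will be calculated for each Lin CCC". A bootstrap tests whether the two CCCs differ. Bland–Altman analysis gives limits of agreement, paired t tests assess mean bias, and multiple linear regression of the deviation from the weighed record looks for predictors of accuracy, among them urban/rural and child or adult. The analyses run first on all index cases together, then by child/adult and by rural/urban.

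The section does not say whether the 3 days are averaged or entered separately. It gives no resampling unit for the bootstrap, and it names no household or person term, robust variance or repeated-measures form.

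**The concern.** The design has two levels of dependence: days within a person, and two people within a household. The article itself describes sources of shared error:

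- Both index cases eat from the same prepared dishes.
- Passive estimates are converted to nutrients in the AIM software with selected food databases, whereas the weighed record goes through Dietplan. A mismatch for one dish therefore enters the passive-minus-weighed difference of everyone who ate it.
- The mathematical volume model uses measurements of household serveware. In its approximate version the shape parameter is picked from 0.5 to 0.8, so an error recurs each time that serveware is used.

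Lin's standard interval, the paired t test and ordinary regression treat every unit as new information. If they are run as named on pooled index cases, bias tests reject too often and agreement intervals cover too seldom. Rural/urban strata still contain both household members. The urban/rural predictor does not vary within a household, so it takes the full effect of clustering.

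**Working it through.** **Plan's own figure.** The article gives no power calculation, standard deviation or intraclass correlation behind 88 households, so there is nothing to reproduce beyond the counts: 88 × 2 = 176 index persons, and 176 × 3 = 528 person-days.

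**Assumptions.** Of the variance of a between-method difference on one person-day, let the household contribute a share *rh* and the person within household a share *rp*. The assumed ranges are *rh* = 0 to 0.3 and *rp* = 0.1 to 0.4. Neither range comes from the document.

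**Design effects (DE) for a mean difference.**
- Pooled person-days: DE = 1 + 5·rh + 2·rp
- Pooled three-day person means: DE = 1 + rh / [rh + rp + (1 − rh − rp)/3]
- Adult-only or child-only, person-days: DE = 1 + 2(rh + rp)
- Adult-only or child-only, person means: DE = 1, since each household gives one value

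True size of a nominal 5% test = 2·[1 − Φ(1.96/√DE)].

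| rh, rp | Pooled person-days: DE, size | Pooled person means: DE, size | One age group, person-days: DE |
|---|---|---|---|
| 0, 0.1 | 1.20, 7% | 1.00, 5% | 1.20 |
| 0.1, 0.2 | 1.90, 16% | 1.19, 7% | 1.60 |
| 0.2, 0.2 | 2.40, 21% | 1.33, 9% | 1.80 |
| 0.3, 0.1 | 2.70, 23% | 1.50, 11% | 1.80 |
| 0.3, 0.4 | 3.30, 28% | 1.38, 10% | 2.40 |

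At 0.2/0.2 the 528 person-days are worth 528/2.40 = 220 independent ones, and the naive standard error is too small by a factor of √2.40 = 1.55. Over the whole grid that factor is 1.10 to 1.82 on pooled person-days and 1.00 to 1.22 on pooled person means.

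**Cross-check with a single correlation.** With 6 person-days per household and correlation 0.1 to 0.3, DE = 1 + 5ρ = 1.5 to 2.5 and the size is 11% to 21%. With 2 person means per household, DE = 1.1 to 1.3 and the size is 6% to 9%.

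**Simulation.** 88 households × 2 persons × 3 days, 2,000 runs, true person-day CCC about 0.84:

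| rh, rp | t-test size: person-days, person means | Lin 95% CI coverage: person-days, person means |
|---|---|---|
| none | 5.0%, 5.1% | 94.5%, 94.3% |
| 0.1, 0.2 | 16.7%, 7.2% | 90.3%, 94.0% |
| 0.2, 0.2 | 21.2%, 9.1% | 88.3%, 93.5% |
| 0.3, 0.2 | 23.3%, 9.4% | 85.3%, 93.3% |

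The CCC interval suffers less than the t test. In the three clustered person-day rows the naive interval averaged 0.047 to 0.048 wide, against a width of 0.056 to 0.064 needed for 95%. A percentile bootstrap that resampled households covered about 92% to 95% (300 runs, so a Monte Carlo standard error near √(0.95 × 0.05/300) = 1.3 points).

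**Where the direction reverses.** Child versus adult is a within-household contrast. Its design effect is 1 + 2·rp − rh on person-days (1.2 at 0.2/0.2) and 1 − rh/[rh + rp + (1 − rh − rp)/3] on person means (1 − 0.2/0.6 = 0.67). On person means the naive standard error is therefore too wide whenever rh > 0.

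**Bland–Altman limits.** Clustering changes the expected pooled variance by about (DE − 1)/(n − 1). With ρ = 0.3 on person-days this is 1.5/527 = 0.3%. The limits barely move; what is misjudged is their precision.

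**The case against.** The strongest reply is that this is a condensed article. The variance estimator, the day-averaging rule and the resampling unit are commonly left to a full protocol or SAP, and neither is shown. The sentence on the CCC interval is compatible with an interval built by resampling households. That reply stands against several stronger readings:

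- A reader might infer that the plan does treat all observations as independent. It never says so; it leaves the unit open.
- A reader might infer that the bootstrap test of passive against recall rejects too often. The resampling unit is not given, and resampling households would handle both levels of dependence.
- A reader might infer that every interval is too narrow. Adult-only and child-only analyses on person means are not affected, and the child–adult regression term can err the other way.
- A reader might work at food-item level. With an assumed 10 items per person-day (60 per household) and correlation 0.05 to 0.1, DE is 1 + 59ρ = 3.95 to 6.9 and the size is 32% to 46%. The article gives neither the item count nor the correlation, and does not say that items are tested individually.
- A reader might assume that one person answers the recall for both index cases. The caregiver answers for small children, but the adult index case is randomly selected and need not be that caregiver.

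It is also fair to say that clustering does not bias the mean differences and hardly moves the CCC estimates, and that the ±10% accuracy rule, as worded, uses neither a p-value nor an interval.

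The reply does not remove the core. The article goes beyond silence: it selects specific tests and applies them first to the pooled index cases. In standard form those tests do not fit the design that Study 3 fixes. Averaging the days reduces the problem in the pooled analyses without removing it, provided there is some household correlation.

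**Conclusion.** The point holds in a limited form. Independent-data methods are named for nested data, and neither the unit of analysis nor the bootstrap resampling unit is fixed. Uncertainty would be understated where adult and child, or repeated days, are pooled: the main index-case analysis, the rural/urban strata, and household-level predictors such as urban/rural.

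The size depends mainly on a choice that the article does not state. With person-days entered separately, it is material for the bias tests and moderate for the CCC intervals. With three-day person means, it is small. Adult-only and child-only analyses then need no correction, but they do need one for repeated days if person-days are used.

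All these figures rest on assumed correlations for the signed difference, and the CCC figures rest on one simulated setting. They show the plausible order of the effect and are not estimates for this study. The point should be settled before the methods are compared, because choosing the unit afterwards could change which results are significant. It does not put the design or the data collection in doubt.

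**What to change.** 1. State the unit of analysis: whether the 3 days are averaged per person or entered as person-days, and at what level portion size is compared.
2. Make the household the resampling unit, keeping all three methods, both members and all days together, for every CCC interval and for the difference between the two CCCs. Some simulated percentile coverages fell nearer 92% than 95%, so an interval on the Fisher-z scale or a bias-corrected one is worth considering.
3. For mean bias, replace the pooled paired t test by a model with household and person random effects, or use household-clustered standard errors. On person means within one age group the paired t test can stay.
4. Use the same random effects or clustered standard errors in the regression. This corrects the urban/rural term and the child–adult term, each in its own direction.
5. If person-days are used, compute the Bland–Altman limits and their confidence intervals in the repeated-measures form.

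The cost is wording and analysis code, with no new data. Pooled intervals become somewhat wider: in the simulated person-day scenarios the CCC interval would widen from about 0.047–0.048 to 0.056–0.064.

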## Discussion

This article describes the protocol of a study designed to assess whether passive dietary intake assessment devices could be used to provide accurate and objective estimates of individual-level dietary intake data in populations at risk of malnutrition. These wearable sensor- and camera-based devices take time-lapse images of food intake passively, and custom software is used to analyze the captured images for dietary intake estimation, thus providing an objective measure. The article describes the proposed devices, their testing procedures, and the use of custom software for nutritional analysis. The study is made possible by the collaboration of nutritionists and engineers and takes advantages of technological advances that make the collection and analysis of data by wearable cameras and associated software possible.

We are validating a comprehensive dietary assessment tool that requires no self-report to assess food preparation and intake in households in Africa. This tool will be validated across different age groups and demographics to take into account the different dietary habits and challenges in accurately assessing dietary intake in different populations. In addition, this study will develop an innovative method of assessing an individual's dietary intake during shared plate eating. Shared plate eating is common in many communities in LMIC but very few methods are available to accurately assess dietary intake of individuals involved in the practice.

Despite the well-intended purpose of using the wearable cameras for dietary data capture, we are aware of the ethical implications of using such devices in households. We have thus taken steps to ensure that the privacy and dignity of participants are maintained at all times during the study. These steps include the inclusion of an image recognition algorithm that distinguishes between food and nonfood images, and the subsequent deletion of all nonfood images in our database. The Foodcam and AIM devices require a special software, only available to study staff, to start the devices and retrieve stored data for added security; this is, however, not available to Ear-worn, eButton, and eHAT. In addition, study participants will be given the opportunity to review the images after collection and can delete any image they feel uncomfortable about sharing.

In conclusion, our study intends to provide low-cost, objective, fast, and accurate methods of collecting and analyzing dietary intake data in populations in LMIC.
